**Discussion:**

The scalability and sustainability of a digital intervention may represent the most cost-effective and feasible approach for LCS programs to proactively engage large numbers of smokers in effective cessation treatment. We will also evaluate the impact and cost-effectiveness of adding proven clinical intervention provided by a TTS. We expect that a combined digital/clinical intervention will yield higher quit rates than digital alone, but that it may not be as cost-effective or feasible for LCS programs to implement. This study is innovative in its use of interoperable, digital technologies to deliver a sustainable, scalable, high-impact cessation intervention and to facilitate its integration within clinical practice. It will add to the growing knowledge base about the overall effectiveness of digital interventions and their role in the healthcare delivery system.

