### Power calculation

Positive (i.e. abnormal) LCS findings increase the odds of abstinence [6, 97–99]. Therefore, to be conservative in our sample size calculations, efficacy estimates for UC are based on data from patients in previous trials with negative screening results. Among patients with negative findings in the National Lung Screening Trial, one-year abstinence rates are in the range of 9.7% [100] to 12.6% [97]. In the Danish Lung Cancer Screening Trial [98], patients received < 5 min of counseling from a nurse and 30-day abstinence at one-year follow-up was 11.4% among patients with no significant LCS findings. Cox et al. [101] reported seven-day abstinence at one year of 13%. Brief counseling for smoking cessation (<3 min) yields six-month abstinence rates of 13.4% [43]. Therefore, we conservatively estimate that biochemically verified abstinence at 12 months for UC will be 10%.

Efficacy estimates for WEB + TXT are based on several converging lines of evidence: (1) two meta-analyses have reported statistically significant effects of interactive and individually tailored interventions compared to usual care or written self-help (relative risk [RR] = 1.48, 95% confidence interval [CI] = 1.11–2.78 [30]; RR = 2.10, 95% CI = 1.25–3.52 [33]; (2) a meta-analysis by Webb et al. [102] found that the use of TXT in Internet interventions had large effects on behavior change (d = 0.81, k = 4); (3) combined Internet and TXT interventions yielded six-month sustained abstinence of 17.1% in Borland et al. [103] and 12-month repeated point prevalence abstinence of 20% in Brendryen et al. [46]. Therefore, we conservatively estimate that biochemically verified abstinence at 12 months for WEB + TXT will be 16%.

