We will compare total and incremental costs to implement each intervention from a payer perspective. Implementation costs of the two interventions will be estimated using average market values for salaries of the additional staff needed to perform the TTS counseling and market costs of the digital intervention. If a treatment effect is observed, we will assess cost per quit and incremental cost per quit. Cost-effectiveness of the two proposed study interventions compared to usual care will be estimated by employing a Markov Model [109, 110]. Hypothetical cohorts representing the U.S. population will be simulated through long-term screening. Disease progression will be modeled with transition probabilities of developing lung cancer. Model parameters not directly measured in the proposed trial will be supplemented with data from the literature, including the publicly available Lung Cancer Policy Model of the Cancer Intervention and Surveillance Modeling Network [111–113]. Model complexity specific to our modeling environment will be determined by available data for the model parameters. A simplistic design not incorporating smoking status (current vs smoker) will be used as the model basis. Smoking status will be incorporated if identified data prove to make this feasible. If not feasible, the simplistic model design will serve as a crucial starting point for further analyses in the future. Sensitivity analyses will be conducted to determine the impact of changes in key model inputs.

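### The long-run Markov analysis names only usual care as comparator, although the stated economic question is the value of adding TTS to the digital programme

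*Protocol article*

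**What the plan says.** Three places in the protocol article bear on this point.

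- **Abstract, Discussion.** The economic question is put as the addition of TTS: "We will also evaluate the impact and cost-effectiveness of adding proven clinical intervention provided by a TTS". The combined arm is expected to produce more quits than digital alone, but "it may not be as cost-effective or feasible for LCS programs to implement".
- **Aim 2 (Implementation) analyses, cost paragraph after Fig. 2, short term.** The plan is "We will compare total and incremental costs to implement each intervention from a payer perspective". Costs will come from "average market values for salaries of the additional staff needed to perform the TTS counseling and market costs of the digital intervention". Then: "If a treatment effect is observed, we will assess cost per quit and incremental cost per quit". No reference arm is named for either incremental quantity.
- **Same paragraph, long term.** "Cost-effectiveness of the two proposed study interventions compared to usual care will be estimated by employing a Markov Model". No comparison of the two active arms is named for the model.

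On effectiveness, the Aim 1 analyses do test all three pairs, including WEB+TXT+TTS against WEB+TXT.

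**The concern.** There are three strategies of increasing intensity, and the article presents the practical choice as digital alone or digital plus TTS. The relevant ratio for that choice is the extra cost of TTS divided by the extra benefit over digital alone. A ratio of the combined arm against UC credits TTS with the gain that the digital programme already delivers. If the digital step is the better value of the two, a costly TTS step is averaged with a cheap digital step and looks better than it is.

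At stake is the long-run figure that screening programmes would use to decide whether to fund TTS. The primary outcome and its analysis are not affected.

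**Working it through.** The article states no cost-effectiveness figure, so there is none to reproduce. The check is whether a ratio against UC can stand in for the ratio of adding TTS.

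**Inputs**
- 12-month abstinence, from the Power calculation section: UC 10%, WEB+TXT 16%, WEB+TXT+TTS 24%.
- D = digital cost per participant over UC; T = added TTS cost per participant. The article gives neither, so both are assumptions.
- D is taken as $67–87. This is the cost per registered smoker that the Background reports from a dental e-referral trial. It is a stand-in, not the market cost that Aim 2 will use.
- T is taken as $200–1,000, which has no source in the article.

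**Cost per extra quit**
- WEB+TXT v UC: D / (0.16 − 0.10) = D / 0.06
- WEB+TXT+TTS v UC: (D + T) / (0.24 − 0.10) = (D + T) / 0.14
- WEB+TXT+TTS v WEB+TXT: T / (0.24 − 0.16) = T / 0.08

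**When does the ratio against UC understate the TTS step?**
T / 0.08 > (D + T) / 0.14 ⇔ 0.14T > 0.08D + 0.08T ⇔ T > 1.33 × D.

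Below that threshold the TTS step is cheaper per quit than the digital step (T / 0.08 < D / 0.06). Digital alone is then removed by extended dominance, and the ratio against UC is the right one. A ranked incremental analysis therefore handles both cases; a fixed UC comparator handles only one.

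**Size at the plan's rates**
Understatement factor = (T / 0.08) / ((D + T) / 0.14) = 1.75 × T / (D + T).
- Lowest: D = 87, T = 200: 1.75 × 200 / 287 = 1.22.
- Highest: D = 67, T = 1,000: 1.75 × 1,000 / 1,067 = 1.64.
- Example: D = 77, T = 300: v UC 377 / 0.14 = $2,693; adding TTS 300 / 0.08 = $3,750; factor 1.39.
- Reversal: D = T = 100: v UC 200 / 0.14 = $1,429; adding TTS 100 / 0.08 = $1,250; factor 0.88.

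**Is T likely to exceed the threshold?**
For D = $67–87 the threshold is 1.33 × D = $89–116 for the whole TTS course. The WEB+TXT+TTS intervention section describes one initial session and four more, so this is about $18–23 per session. The article's Discussion, on why digital was not tested as an add-on to TTS, describes TTS as markedly more expensive and digital enrolment as markedly cheaper. The direction is probable, but no figure in the article establishes it.

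**Sensitivity outside the plan's rates**
If the combined arm reached only 20%, the factor would be (0.10 / 0.04) × T / (D + T) = 1.74–2.34. At 18% it would be (0.08 / 0.02) × T / (D + T) = 2.79–3.75. These replace the planned 24% and show only that the masking grows as the TTS gain shrinks.

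**The case against.** The strongest reply is that the TTS increment is already planned. The same paragraph promises incremental costs and "we will assess cost per quit and incremental cost per quit", costs TTS staff separately from the digital programme, and follows an effectiveness plan that tests the active pair. A reader might infer from the Markov sentence that the value of adding TTS is not estimated at all. The article does not support that: the short-term increment may well be covered, since an unnamed reference arm is not an excluded one. If the model reports costs and effects by arm, the long-run ratio also follows by subtraction. What remains is that the short-term quantity depends on a treatment effect being seen and has no long-run outcome, and that the article does not commit to reporting the model by arm.

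A reader might also infer that the planned figure is biased in favour of TTS as a matter of fact. That does not hold either. It requires T > 1.33 × D, and the direction reverses when the two costs are equal.

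Two further objections have weight. The illustration is in cost per quit, whereas the Markov model concerns disease progression and its base design does not carry smoking status; no size can be given for the model's own output. And a journal article may leave the reference arm and ranking rules to a fuller document. The silence on the reference arm for cost per quit is therefore not a fault in itself. The Markov comparator is different, because the article states it outright and it does not match the article's own question.

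**Conclusion.** The point holds in a limited form. The article names UC as the only comparator for the long-run model, while its abstract asks about adding TTS to the digital programme. A ratio against UC pools a 6-point digital gain with an 8-point TTS gain and does not answer that question.

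At 10/16/24% it understates the cost per extra quit of adding TTS if T > 1.33 × D, by 1.2 to 1.6 fold under the assumed D of $67–87 and T of $200–1,000. The size rests on those assumed costs and on cost per quit as the measure. The mismatch of comparators rests on neither. It should be corrected, but it is a matter of stated comparison and reporting; no data are lacking.

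**What to change.** Change the Markov sentence to a fully incremental analysis of the three strategies:

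- Show costs and effects for each arm, UC included.
- Rank the strategies by cost and remove any that are dominated, including by extended dominance.
- Report WEB+TXT v UC and WEB+TXT+TTS v WEB+TXT. Where the ranking removes a strategy, say so and give the ratio against the next remaining one.
- Name the same comparisons for the within-trial incremental cost per quit.
- Keep the ratios of each intervention against UC as supplementary results.

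The cost is a change of wording and a few more lines of model output, with no new data. The downside is that the TTS figure will probably look less favourable than the ratio against UC.

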## Background

Lung cancer screening (LCS) provides a unique opportunity to deliver tobacco dependence treatment on a population-wide basis. More than 4 million current smokers age 55+ years are likely to be eligible for LCS [1, 2]. LCS saves lives through early identification of lung cancer. However, given that most lung screens are negative [2] and that smoking causes 11 other types of cancer as well as cardiovascular disease and other lung disease [3], the health benefits of providing effective tobacco dependence treatment for LCS patients are far-reaching. Smokers seeking LCS report interest in quitting and receiving cessation services [4–8] and simulation models predict that tobacco dependence treatment can improve the cost-effectiveness of LCS by 20–50% [9, 10]. Delivering tobacco dependence treatment that is feasible within a LCS program is crucial for maximizing the health benefits of screening [11, 12].

The Centers for Medicare and Medicaid Services (CMS) requires that LCS include a shared decision-making visit with smokers that includes “counseling on the importance of smoking cessation and furnishing of information about tobacco cessation interventions” [13]. This approach is analogous to the Ask–Advise–Refer (AAR) model of tobacco dependence treatment [6] in which healthcare providers ask about smoking status, advise a smoker to quit, and refer to readily available cessation treatment resources. A recent study by Ostroff et al. [14] reported that the majority of LCS programs “always” ask patients about smoking status (98.9%) and advise current smokers to quit (91.4%) but fewer reported delivery of cessation counseling (57%) or referral to a quit line (60.2%). Low rates of treatment referral in LCS programs are consistent with data from other healthcare settings [15–17]. Additionally, most smokers passively referred to treatment fail to follow through [15–18]. As noted by Fucito et al. [19], “patient motivation as a requirement for treatment (i.e. an opt-in model) means that most smokers will not receive smoking-cessation assistance” (page 9). Other treatment models are needed to address smoking cessation in the LCS setting.

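### The cost-effectiveness model names lung cancer as its only disease process and leaves smoking status out of its base design, so a quit gets no modelled health benefit, or only the lung cancer part of it

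*Protocol article*

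**What the plan says.** The Aim 2 (Implementation) analyses section plans two kinds of economic result. The first is cost per quit and incremental cost per quit, if a treatment effect is seen. The second is a model: "Cost-effectiveness of the two proposed study interventions compared to usual care will be estimated by employing a Markov Model". On its structure the article says:

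- Disease process: "Disease progression will be modeled with transition probabilities of developing lung cancer". No other smoking-related disease and no death from other causes is mentioned. The one outside source named for parameters is a lung cancer policy model.
- Base design: "A simplistic design not incorporating smoking status (current vs smoker) will be used as the model basis".
- Extension: "Smoking status will be incorporated if identified data prove to make this feasible". If that is not feasible, the simpler design stands as a starting point for later work.
- Flexibility: "Model complexity specific to our modeling environment will be determined by available data for the model parameters". Sensitivity analyses are planned on key model inputs; no alternative structure is named.

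The Background makes the case for cessation in lung screening on a wider base. It notes that "most lung screens are negative" and that "smoking causes 11 other types of cancer as well as cardiovascular disease and other lung disease", and concludes that "the health benefits of providing effective tobacco dependence treatment for LCS patients are far-reaching".

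**The concern.** A cessation programme changes health by changing smoking status. A model that values such a programme needs a state that a quit can alter, and transitions that depend on that state. The base design has no such state. The only transition named covers one of the diseases on which the Background relies.

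Cost-effectiveness is one of the article's main messages. The abstract expects the combined arm to give more quits than the digital arm but perhaps not to be as cost-effective. If the model counts the full cost of each intervention and only part of the benefit of each quit, its result leans against both interventions. The shortfall in health gain is larger, in absolute terms, for the arm with more quits. A decision-maker could read the result as poor value when the cause is the model boundary.

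**Working it through.** The article states no cost-effectiveness ratio, so there is no figure to reproduce. The check has three steps.

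**1. Base design without smoking status.** Let Δq be the difference in quit rates between two arms, g the health gain per quit and ΔC the cost difference. The incremental ratio is ΔC / (Δq × g). From the Power calculation section, the assumed abstinence rates are 10% (usual care), 16% (WEB + TXT) and 24% (WEB + TXT + TTS). So Δq against usual care is 16 − 10 = 6 points and 24 − 10 = 14 points. If the transitions do not depend on smoking status, g = 0. Then Δq × g = 0 for both comparisons and the ratio is undefined, whatever quit rates the trial finds.

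**2. Extension with smoking status, lung cancer transition only.** Let s be the share of the true gain that comes through lung cancer. The model uses s × g in place of g, so with costs unchanged the ratio is multiplied by 1/s. The documents give no s. Over an assumed range:

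| s | 1/s |
|---|---|
| 0.1 | 10.0 |
| 0.2 | 5.0 |
| 0.3 | 3.33 |
| 0.5 | 2.0 |
| 0.7 | 1.43 |
| 0.9 | 1.11 |

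**3. What s might be.** All inputs here are assumptions; none stands in the documents. A discounted cohort runs for 20 years at 3%. The annual death probability is

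d = I × F × RR_LC + M × RR_OC,

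where I is lung cancer incidence, F its fatality, M death from other causes, and RR_LC and RR_OC the relative risks after quitting. Discounted life-years are the sum over t = 0 to 19 of ((1 − d)/1.03)^t.

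Central inputs: I = 0.7%, F = 65%, M = 2.2%, RR_LC = 0.6, RR_OC = 0.7.

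- Continuing smoker: d = 0.007 × 0.65 + 0.022 = 0.02655.
- Quitter, lung cancer effect only: d = 0.00455 × 0.6 + 0.022 = 0.02473.
- Quitter, both effects: d = 0.00273 + 0.022 × 0.7 = 0.01813.
- Gain over the continuing smoker: 0.178 life-years (lung cancer only) and 0.856 (both). So s = 0.178/0.856 = 21%, and 1/s = 4.8.

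Ranges: I 0.2–1.0%, F 60–70%, M 2.0–2.5%, lung cancer risk lowered 30–50%, other-cause death lowered 20–40%.

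| Case | I | F | M | Lung cancer risk lowered | Other-cause death lowered | s | 1/s |
|---|---|---|---|---|---|---|---|
| Lowest | 0.2% | 60% | 2.5% | 30% | 40% | 3% | about 30 |
| Central | 0.7% | 65% | 2.2% | 40% | 30% | 21% | 4.8 |
| Highest | 1.0% | 70% | 2.0% | 50% | 20% | 46% | 2.2 |
| Highest, smaller other-cause benefit | 1.0% | 70% | 2.0% | 50% | 10% | 63% | 1.6 |

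The last row lies outside the assumed ranges. It shows how far s depends on the benefit given to other causes of death.

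**The case against.** The strongest reply is that this is one paragraph of a condensed article. It does not say that lung cancer is the only process, or that death from other causes is absent or equal by smoking status. It ties complexity to available data, draws parameters from the literature and plans sensitivity analyses. Death states may be set out in a fuller document that is not shown. That much stands: the article supports saying that lung cancer is the only disease process named, and no more. But the point does not rest on silence. The article states how disease progression will be modelled and that the base design leaves out smoking status. The one extension it names is smoking status, which by itself would not add other diseases.

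A second reply is that the Background explains why cessation matters and sets no model boundary, and that a narrow model can be a deliberate conservative choice. That is fair, but the article does not present it as one. A conservative scope would also need smoking status in the model, or there is no gain to be conservative about.

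Third, the article does not name life-years as the model's unit, and cost per quit is planned alongside without using the disease model. Both are correct. Life-years serve only as an illustration here, and the cost-per-quit results are untouched.

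A reader might go further and infer that most of the benefit of a quit is left out. The documents do not support that. They give no split of benefit by disease, and whether s falls below one half depends on assumed inputs, as the 63% case shows.

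**Conclusion.** The point holds in two parts. In the base design, a quit has no stated route to any modelled health benefit, lung cancer included. This follows from the text and needs no outside figure. If smoking status is added, the named transition credits a quit only through lung cancer, so the health gain is understated and the modelled cost-effectiveness is biased against both interventions.

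The size of the second part is unknown. Under the assumed ranges the captured share is about 3% to 46% (21% centrally), and it can pass 50% if quitting does less for other causes of death. The direction rests on two premises: that quitting lowers harm from the other diseases the Background lists, and that incremental costs stay as modelled. Costs of care in added years of life could offset some of the change in the ratio.

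The primary outcome, the sample size and the cost-per-quit results are not affected.

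**What to change.** Before the economic analysis starts, amend the model description as follows:

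1. Put smoking status, current versus former, in the base-case model. State that the trial's quit rates set the distribution between the two and that the transitions depend on it. The article's parenthesis describing smoking status should be corrected at the same time, since its two labels do not form a contrast.
2. Add death from other causes that differs between current and former smokers, taken from published mortality by smoking status.
3. Keep the lung-cancer-only version as a scenario, labelled as a conservative estimate of the interventions' value.
4. Vary the other-cause mortality input in the planned sensitivity analyses.

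The cost is a little more modelling work and one more literature input to vary. No trial data, visits or patients are involved.

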#### Aim 3 (Reach and Adoption) analyses

Reach will be evaluated as the representativeness of the enrolled sample relative to all smokers that are assessed for LCS eligibility. We will compare the enrolled sample to those that are assessed for LCS eligibility on available demographic, smoking history, and medical history variables using Chi-square tests and T-tests.

Adoption will be assessed through a mixed mode quantitative/qualitative approach. We will conduct an enterprise-wide survey of LCS program directors and other key informants (e.g. nursing staff, office managers) in all LCS facilities within Mayo Clinic. The survey will gather detailed information about the barriers that would impede adoption of the digital and combined digital/clinical treatments evaluated in this study, as well as the organizational processes or resources that would facilitate their adoption and implementation. We will also conduct structured interviews with members of the Mayo Clinic Lung Screening Program to gather in-depth information about the feasibility of these treatment approaches and site-specific recommendations about their implementation.

### Protocol amendments

Changes to the research protocol will be reviewed by the Institutional Review Board (IRB). Amendments will be made to the trial registry as necessary.

### Confidentiality

The data management will be governed by standard procedures with regard to data security and access. All analyses are logged with respect to IRB authorization, accounting information, principal and secondary investigators, statistician, and data analyst involved in the analysis.

BecomeAnEX has stringent privacy and security policies in place which include a comprehensive privacy policy, strong encryption used in the transmission of all health-related information, electronic access controls on all personally identifiable information, and industry standard network protection. All information collected via the Internet will be kept secure in transit using the Secure Socket Layer (SSL) protocol. Both the BecomeAnEX WEB and TXT systems are cloud hosted platforms and have security audits performed annually. All communications between users and BecomeAnEX.org, and between BecomeAnEX.org and the TXT system, are sent securely via https. Both systems maintain offline backups stored in geographically separate areas for disaster recovery. All data transferred to and from the study sites will be de-identified and uploaded using a secured transfer protocol. All data will be stored in a database subject to both physical and electronic protection. The BecomeAnEX Privacy Policy is available at http://www.becomeanex.org/privacy-policy.php and will be in effect for all participants that register on the website.

